## Abstract

**Background:**

Anxiety disorders are common and debilitating which is why treatment is so important. According to the guidelines, Cognitive Behavioral Therapy (CBT) has the highest level of effectiveness among psychotherapeutic treatments and is the recommended procedure. However, not everyone responds well or at all to CBT which makes a wider range of therapy options valuable. Positive Psychotherapy (PPT) comes to mind as an alternative with its strength-based approach focusing on enhancing well-being and life satisfaction. Additionally, it has not yet been extensively studied how the processes that occur during treatment sessions and between treatment sessions effect treatment outcome. Thus, to lessen the lack of evidence regarding the efficacy of PPT as an anxiety treatment the planned study examines and compares the effectiveness of CBT and PPT as well as the effect of intrasession and intersession processes of the two therapy approaches.

**Method:**

The study is in the planning stage and consists of an efficacy and a process study. The efficacy study is a randomized controlled comparative study of patients with anxiety disorders (generalized anxiety disorder and/or panic disorder with or without agoraphobia) with two active treatment conditions (PPT and CBT) and a control group (CG; positive psychotherapy with minimal therapeutic supervision) in an online group setting. There are three measurement time points: before treatment begins (T0), at the end of the ten-week treatment (T1), and a follow-up after three months (T2). The aim of the study is to evaluate the efficacy of PPT and CBT in the treatment of anxiety disorders, and to compare the efficacy of online-based PPT with minimal therapeutic supervision and online-based PPT with intensive therapeutic supervision in the treatment of anxiety disorders. The process study will be used to evaluate both the intrasession processes and the intersession processes of the therapy in the two intervention groups. In addition, the process variables that predict the success of the therapy and the extent to which PPT and CBT differ in the therapy processes will be tested. The study is registered at the German Clinical Trial Register (№ DRKS00027521).

**Discussion:**

To our knowledge, this is the first randomized controlled comparative study to examine the effectiveness of CBT and PPT for anxiety disorders in an online group setting.

## Introduction

### Anxiety disorders—Epidemiology and treatment approaches

Anxiety disorders are more widespread and represent one of the most common mental disorders [1, 2]. According to international studies, the lifetime prevalence ranges between 14% and 29% [2, 3], whereby the quality of life of those affected is often severely restricted. With regard to the so-called “Years Lived with Disability” (YLD), i.e. the years of life lived with disability, according to the World Health Organization (WHO) in 2015 anxiety disorders are in sixth place worldwide. They are thus primarily chronic diseases [4]. Anxiety disorders are associated with a high utilization of the health care system [5] and extremely comorbid with other mental illnesses [6, 7], such as depression and alcohol dependence [8]. According to the S3 guidelines for the treatment of anxiety disorders, psychotherapy and pharmacotherapy ought to be offered equally. After giving thorough information about the various treatment options, the patient’s preference should be considered. For all anxiety disorders, CBT has the highest level of evidence and recommendation of all psychotherapeutic methods. In the case of insufficient effectiveness of one form of therapy, the other or a combination of both should be offered [5, 9]. Psychodynamic psychotherapy has been included in the current S3 guidelines, with the recommendation that this form of psychotherapy be offered when CBT has proved ineffective, is not available or when there is a preference for it on the part of the informed patient [5].

### Positive psychotherapy

PPT is a science-based psychotherapy that enhances positive emotions, character strengths, and meaning-making in a direct way, with the goal of reversing psychopathologies and promoting the experience of happiness [10]. In contrast to traditional deficit-oriented treatment models, PPT strives to focus on human well-being and satisfaction. The central assumption is that the evocation and promotion of positive emotions, the awareness of one’s own strengths and the sense of meaning are particularly efficient in the treatment of mental disorders, as people are subject to the so-called negativity bias, especially in stressful life situations. This negativity bias describes the phenomenon that negative thoughts, feelings and experiences have a greater psychological impact than neutral or positive ones [11]. PPT strives to compensate for this bias by focusing attention on positive things. According to [12], a lack of positive emotions and well-being can not only be a symptom but also a cause of mental disorders.

### Previous efficacy studies on positive psychotherapy

Before PPT was evaluated as an integrated treatment concept, individual interventions were empirically validated [13]. Individual Positive Psychology interventions have been shown to improve psychological well-being, promote hope and enjoyment, advance psychological rehabilitation and self-esteem, and positively influence psychopathological symptoms [13, 14]. In a meta-analysis of the effectiveness of positive psychology interventions, [15] found small to moderate effects on well-being, strengths, quality of life, depression, anxiety, and stress. Numerous studies regarding the effectiveness of positive-psychological interventions conducted on the disorder depression demonstrated a significant reduction in symptoms and an increase in well-being [13]. [14] found that individual PPT with severely depressed patients resulted in symptom improvement and longer remissions compared to usual care including medication therapy. Several studies have demonstrated moderate to strong effects in moderate to severe disorder severity, as well as remission rates of up to one year compared to waiting list control groups or patients treated with antidepressants and psychiatric monitoring [12, 16–18]. For depression disorder PPT is also highly effective when compared to CBT, as shown in the randomized-controlled comparative study by [19]. Their results revealed large effects for the reduction of depressive symptomatology, while only small to medium effect sizes were found for CBT. PPT was also superior to CBT in terms of positive outcomes such as life satisfaction and subjective well-being. Additionally, PPT lead to significant effects in the treatment of borderline patients [20] as well as in the treatment of nicotine dependence [21]. In summary, based on the studies conducted to date, it can be assumed that PPT is an effective method for several different psychological disorders.

### Intrasession and intersession processes

According to [25, 26], the process research phase in psychotherapy represents the fourth and current phase of psychotherapy research. It was preceded by the legitimation phase, the competition phase and the prescription phase. Process research is concerned with investigating the mechanisms of action of psychotherapeutic treatments. Intrasession processes refer to all those changes that occur directly in response to specific events in the therapy session. Whereas intersession processes are defined as conscious processes of change between two sessions that are brought about by representations of the session [27]. [28] showed that approximately 90% of all patients engage with therapy or their therapist between sessions. Patients who are more intensely involved in the therapeutic process also show more intense representations [29, 30] and a better therapy outcome [31]. It has also been shown that patients’ positive perceptions of therapy progress are associated with greater involvement in intersession process thoughts and actions [32]. A clear correlation between positive representations and a good therapeutic relationship has been found [33–36].

### Effectiveness of video-assisted therapy

The importance of virtual care has grown strongly especially due to the Covid-19-Pandemic. Additionally, video-assisted therapy is becoming increasingly important and has been used more frequently. In a large-scale meta-analysis, online interventions from 108 randomized controlled trials for 25 different clinical impairments were examined from the period 2000 to 2012 [37]. Consequently, the effectiveness of online therapy for depression, social phobia, and panic disorders can be considered empirically proven. Further studies are available for eating disorders [38], pathological gambling [39], complicated grief [40], substance-related addictions [41] and post-traumatic stress disorders [42], anxiety [43] and functional disorders [37], among others. The results of internet-based interventions are promising. For depression, reported effect sizes from five meta-analyses range from *d* = 0.41 to *d* = 0.94 [44], and online programs for anxiety disorders have an average symptom reduction of *d* = 0.92 [45]. These results show that online treatments lead to the same neuronal changes as those observed after successful classical psychotherapy [46]. Another meta-analysis on the effectiveness of online psychotherapy, which included 92 studies with a total of 9764 participants, showed that the mean treatment effect (Cohen’s *d*) between pre- and postmeasurement was 0.53, averaged across all disorders and forms of intervention. This effect size is quite comparable to that of conventional outpatient therapy [47]. [48] found that both video-based therapy and traditional therapy achieved particularly good effects. Therapeutic success with video-assisted therapy is strongest when using the CBT treatment modality and for anxiety, depression, and Post-Traumatic Stress Disorder. [49] conducted a study of adolescents with anxiety disorders. While one group received a face-to-face intervention, the other group received video-assisted therapy with less therapeutic support. Both groups showed a significant decrease in anxiety symptomatology, even when compared to a waitlist control group. These effects persisted over time (12-month follow-up). Computer-assisted CBT for anxiety showed similar clinical outcomes to face-to-face psychotherapy [50, 51].

## Methods

### Design and setting

The planned study is a randomized-controlled comparative study and will be realized as a ten-week online group therapy with the following three treatment conditions to which participants will be randomly assigned: Group 1: An intervention condition in which participants receive PPT treatment, Group 2: an intervention condition in which they receive CBT treatment, and Group 3: a control condition designed as PPT treatment with minimal therapeutic supervision. Participants in the control condition receive the same material, content, and exercises as the participants in PPT treatment condition. However, they only have three online video call meetings and work through the content on their own during the remaining weeks. There are three measurement time points for testing the efficacy hypotheses: An online questionnaire survey before treatment begins (PRE measure), a second identical survey after treatment will be completed (POST measure), and a third identical survey three months after treatment will be ended (FOLLOW-UP measure). This results in a 3×3 between- and within-subjects design. The hypotheses regarding the intra- and intersession processes will be tested by means of weekly surveys in each case before the therapy sessions (intersession processes) as well as after the therapy sessions (intrasession processes). Fig 1 shows the study design and the different steps of the procedure in a chronic flow diagram. The study is conducted at the Department of Clinical Psychology and Psychotherapy at the University of Salzburg. Prior to initiation, the study design was submitted to and approved by the Ethics Committee of the University of Salzburg (EK-GZ: 22/2021). The study is registered at the German Clinical Trial Register (№ DRKS00027521; date of registration February, 3^rd^ 2022; type of registration: prospective). The full details according to the World Health Organization Trial Registration Data Set standards are shown in Table 1. For a complete description of the relevant information and their position in the manuscript according to the SPIRIT checklist, please refer to S1 Checklist.

**Fig 1 pone.0299803.g001:**
[figure not shown]
Flow diagram of the study design.

**Table 1 pone.0299803.t001:** Items from the World Health Organization Trial Registration Data Set.

Data Category	Information
Primary registry and trial identifying number	German Clinical Trials Register № DRKS00027521
Date of registration in primary registry	February, 3^rd^ 2022
Secondary identifying numbers	N/A
Source(s) of monetary or material support	Financial contributions from the Paris Lodron University of Salzburg, Austria
Primary sponsor	Stiftungs- und Förderungsgesellschaft der Paris Lodron Universität Salzburg, Austria
Secondary sponsor	N/A
Contact for public queries	Paris Lodron Universität Salzburg, Austria, [name], [contact], e-mail: [contact]
Contact for scientific queries	Univ.-[name]. [name], Paris Lodron Universität Salzburg, Austria
Public title	Positive Psychotherapy and Cognitive Behavioral Therapy in Anxiety Patients
Scientific title	Positive Psychotherapy and Cognitive Behavioral Therapy in Anxiety Patients—A randomized controlled Trial with three Conditions in an online Group Setting
Countries of recruitment	Austria, Germany
Health conditions or problems studied	ICD10: F41.1 Generalized anxiety disorder, F41.0 Panic disorder [episodic paroxysmal anxiety], F40.1 Social phobias
Intervention(s)	Active comparator 1: Positive psychotherapy, Active comparator 2: Cognitive behavioral therapy, Control group: online positive psychotherapy with minimal therapeutic supervision
Key inclusion and exclusion criteria	Ages eligible for study: between 18 and 65 years, Sexes eligible for study: both, Inclusion: sufficient intellectual capacity and knowledge of the German language, presence of one of the following disorder diagnoses according to F41.0 panic disorder with and without agoraphobia and/or, F41.1 generalized anxiety disorder and/or, F40.1 social phobia, Exclusion: concurrent or planned participation in psychotherapeutic or psychological treatment or counseling or participation in other psychological group services in the following three months, presence of one or more of the following disorders: major depressive episode, bipolar affective disorder or mania (current as well as history), schizophrenic or schizoaffective disorder, grief reaction, severe anorexia or bulimia, substance dependence (alcohol, illicit drugs), severe Personality Disorder; acute suicidality; use of psychotropic drugs itself not a criterion for exclusion, but a change in medication, a change in dose, or complete discontinuation of the drug in the past or next three months
Study type	Interventional, randomized control study, masking: none, primary purpose: comparative therapy quality assessment
Date of first enrollment	Planned: March, 1^st^ 2022
Target sample size	165
Recruitment status	Recruiting
Primary outcomes	Extent of anxiety, subjective experience of happiness, quality of life
Key secondary outcome	General psychological distress

### Feasibility

The feasibility of the study design was examined as part of a master’s thesis by one of the study assistants. For this purpose, the first study round was evaluated for the effectiveness and feasibility of the interventions, as well as the satisfaction with the therapy from the perspective of the participants and therapists. The results of the work showed high feasibility of the study design, high satisfaction with the therapy, and trends indicating effectiveness of the treatment for anxiety disorders. The detailed results of the feasibility study can be found in the master’s thesis of [52].

### Participants

This trial will include patients who meet the following criteria. Inclusion criteria:

age between 18 and 65 yearssufficient intellectual capacity and knowledge of the German languagepresence of one of the following disorder diagnoses according to ICD-10
F41.0 panic disorder with and without agoraphobia and/orF41.1 generalized anxiety disorder and/orF40.1 social phobia

Exclusion criteria:

concurrent or planned participation in psychotherapeutic or psychological treatment or counseling or participation in other psychological group services in the following three monthspresence of one or more of the following disorders: major depressive episode, bipolar affective disorder or mania (current as well as history), schizophrenic or schizoaffective disorder, grief reaction, severe anorexia or bulimia, substance dependence (alcohol, illicit drugs), severe Personality Disorderacute suicidalityuse of psychotropic drugs itself not a criterion for exclusion, but a change in medication, a change in dose, or complete discontinuation of the drug in the past or next three months

### Sample size

The sample size was calculated using a power analysis (G*Power 3.1; [53]), given an alpha error of.05 and a power ≥.80, resulting in a sample size of *N* = 165. Accordingly, 55 persons would be included in each of the three intervention groups. Effect size estimates resulted from findings of previous studies [12, 19]. Since a high dropout rate is to be expected, a significantly higher number of subjects will be screened and admitted to the study.

### Participant recruitment process

Recruitment will be conducted using a variety of strategies. Part of the recruitment will be done by distributing flyers in pharmacies, doctors’ and psychotherapists’ offices, and other public buildings such as universities, churches, supermarkets, and schools. In addition, clinics, physicians, and psychotherapists will be contacted directly by mail and asked to make patients aware of our offer. At the same time, the study will be advertised online via various social media channels. On the one hand, Facebook is used to post in disorder-specific groups and make those who are affected aware of our offer directly. Instagram is the second platform we will use to promote the study. To do this, an Instagram page will be created for the study. Through this page, various influencers related to the study topic will be contacted via direct message and asked to use their reach and share the study. In addition, own topic-related posts will be created and shared, and advertisements will be placed for the posts. Interested people can contact us via mail to the study mail address, which was communicated via the various advertising tools. To check the general suitability for the study and to filter out suitable participants, interested people will undergo a pre-screening form, which was carried out in the form of an online questionnaire. Based on the evaluation of the pre-screening questionnaire and previously determined cut-off values, a screening appointment will be arranged with suitable applicants. Unsuitable applicants will receive a rejection by e-mail which includes contact details for psychotherapeutic support services. The screening will take place via an online video call using the provider Zoom. It will be conducted by psychologists and master psychology students employed within the study project. In the screening, the German version of the short form of the Diagnostic Interview in Psychological Disorders (MINI-DIPS; [54]) and the German version of the Personality Disorder Screening—Short Form (PSS-K; [55]) will be used to check inclusion as well as exclusion criteria and to formulate a diagnosis. In addition, information about the procedures and contents of the study and the various data collection procedures will be given, and informed consent will be obtained from the participants to participate in the study and to complete the mandatory evaluation questionnaires. All participants will be also given the telephone number of the crisis service responsible for their area so that they can contact them in the event of an emergency.

### Randomization and blinding

With the help of the online platform randomizer.org participants will be randomly allocated to three test conditions right after they completed the PRE-evaluation form. The allocation is random and independent of the diagnosis or other criteria. The externally recruited therapists will be blindly assigned to the treatment conditions. Neither the participants nor the practitioners were allowed to decide which group they were assigned to. The authors, who also act as therapists, will conduct the control group to prevent falsification effects in the intervention groups. Statistical analyses will be conducted by the principal investigator, who will not be blinded or independent.

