#### Primary outcome measures

extent of anxiety as measured by self-report questionnaires
Beck Anxiety Inventory German version (BAI; [57])Panic and Agoraphobia Scale German version (PAS; [58])Generalized Anxiety Disorder 7 German version (GAD-7; [59])Fear Questionnaire German version (FQ; [60])subjective experience of happiness
Positive Psychotherapy Inventory German version (PPTI; [10])Flourishing Scale German version (FS; [61])quality of life
Satisfaction with Life Scale German version (SWLS; [62])

For additional third-party assessment of the level of anxiety a questionnaire designed by the authors was used (the following topics were queried: tension, anxious mood, fear, sleep disturbance, depressiveness, anxious behavior, physical symptomatology, psychological distress, impairment in living, life satisfaction, motivation & energy).

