### Trial governance

The Trial Management Group consists of the principal investigator, the study director ([name]) and is supported by two study assistants. The Management Group will provide overall management of the study including set-up of the study, recruitment, managing mails, and interpretation of results. In addition, eleven therapists (psychological psychotherapists in training) support the study by conducting the therapy groups. In preparation for the study, therapy manuals, websites and workbooks were developed for the different intervention groups by the principal investigator, the study director and a study assistant. Overall supervision of the trial is provided by the principal investigator. The therapists were trained in the manuals and for screenings by the project management. All therapists were trained in both manuals in order to be able to adopt both intervention groups (PPT and CBT) as needed during the course of the various study runs. At regular intervals, the therapy sessions are checked for their manual compliance and the therapists receive supervision by qualified psychotherapists and supervisors.

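### Allocation ignores diagnosis and the stated primary analysis does not adjust for diagnosis or run, so chance imbalance on a likely prognostic factor is left uncorrected; the cost is precision and credibility, not bias

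*Protocol article*

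**What the plan says.** All places are in the protocol article.

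- **Randomization and blinding:** an online randomiser assigns each person to one of the three arms once the baseline questionnaire is done. On what the assignment may depend, the section says: "The allocation is random and independent of the diagnosis or other criteria". It does not say whether the sequence is simple, blocked or a fixed-size list. It also says that the principal investigator will analyse the data and will be neither blinded nor independent.
- **Sample size:** "Accordingly, 55 persons would be included in each of the three intervention groups". More people than this are to be admitted because many dropouts are expected.
- **Participants:** any of panic disorder, generalized anxiety disorder or social phobia qualifies, and a person may have more than one. Under Participant recruitment process, the MINI-DIPS interview that fixes the diagnosis takes place at screening, before allocation.
- **Primary outcome measures:** the anxiety scales include "Panic and Agoraphobia Scale German version (PAS; [58" and the GAD-7.
- **Interventions and Trial governance:** treatment is given in groups, with two-person teams in every condition. Therapists are trained in both manuals so that they can cover either "as needed during the course of the various study runs".
- **Statistical analysis:** a repeated measures ANOVA in which the three arms are the only stated between-group factor.

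**The concern.** The sentence on allocation is a stated choice, not a silence. A fuller protocol could add detail on the sequence, but it could not stratify by diagnosis without contradicting this sentence.

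The choice fits this trial poorly. A person without panic disorder has little PAS score to lose, and the same may hold for the GAD-7 in a person without generalized anxiety. Diagnosis may therefore affect the amount of change as well as the starting level, and a pre-post comparison removes only the second. If the arms differ by chance in diagnosis, part of the difference in mean change reflects case mix, and the stated model does not take it out.

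Run matters for a related reason. Each run supplies participants for group treatment, so uneven allocation within a run would make group size differ between arms.

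**Working it through.** **1. The plan's own figure.** 165 / 3 = 55, which agrees with the article. N = 165 itself cannot be reproduced, because no effect size or correlation is given. It is plausible: a repeated measures ANOVA for the between-group factor with assumed f = 0.20 and correlation 0.5 gives exactly 165. Nothing below disputes N.

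**2. Imbalance in diagnosis.** The case mix is not stated, so the share q is assumed at 20% to 50%. With 55 per arm, the SD of the difference in share between two arms is √(2q(1−q)/55):
- q = 0.20: √(0.32/55) = 7.6 points
- q = 0.50: √(0.50/55) = 9.5 points

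Simulated chance of a difference of 15 points or more (at least 9 people of 55 when arms are fixed):

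| Share q | Some pair, arms fixed at 55 | Some pair, simple allocation of 165 | One named pair, arms fixed at 55 |
|---|---|---|---|
| 20% | 10% | 12% | 4% |
| 33% | 20% | 22% | 8% |
| 40% | 22% | 25% | 10% |
| 50% | 24% | 26% | 10% |

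The range for some pair is therefore 10% to 26%. It hardly depends on whether the sequence is simple or blocked for size.

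**3. What such an imbalance does.** If people with and without a diagnosis differ in mean change by δ, a 15-point imbalance shifts the difference between two arms by 0.15 × δ. The documents give no δ. If δ were as large as the effect detectable with 80% power in step 4 (0.534 SD), the shift would be 0.15 × 0.534 = 0.08 SD.

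**4. Arm sizes overall, if allocation is simple (assumed).** Expected size is 55 per arm, with SD √(165 × 1/3 × 2/3) = 6.1 and a 95% range of 43 to 67.
- P(exactly 55/55/55) = 165! / (55!³ × 3¹⁶⁵) = 0.5%
- P(smallest arm ≤ 50) = 65%; P(smallest arm ≤ 45) = 17%

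The power cost is small. The difference that gives 80% power at 55 v 55 is d = (1.960 + 0.842) × √(2/55) = 0.534. Averaged over simple allocations, pairwise power is 79.5% (2.5th percentile 74.7%), and omnibus power, set to 80% at equal arms, is 79.6%.

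**5. Arm sizes within a run, if allocation is simple.** Run size is not stated, so a range is shown:

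| Run size (assumed) | One arm at least twice another | Smallest arm ≤ 5 |
|---|---|---|
| 24 | 43% | 40% |
| 30 | 33% | 11% |
| 36 | 25% | 2% |

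**6. Effect of blocking.** Assume 5 runs of 33 and three equally common, non-overlapping diagnoses. Blocks of 3 within run give 11 per arm per run and exactly 55/55/55. Blocks within run and diagnosis leave a mean gap of 3.1 between the largest and smallest arm, with the smallest averaging 53.5. Simple allocation gives a mean gap of 12.5 and a smallest arm averaging 48.8. Blocking within run alone therefore brings the whole gain in arm size.

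**The case against.** The strongest reply is that unstratified randomisation of 165 people is legitimate. Chance imbalance is already covered by the type I error rate. Baseline PAS and GAD-7 are measured, and the outcome is change, so differences in starting level largely drop out. For one named pair of arms, a 15-point imbalance has a chance of only about 4% to 10%. That the scales respond differently by diagnosis is a reasonable expectation from what they measure, but the documents do not show it. All this stands. It limits the point to precision and credibility, and it does not explain why a factor already recorded is left out of the model.

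Three stronger readings are tempting and are not supported:

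- **That the scheme cannot deliver 55 per arm.** Equal-probability allocation has an expected size of exactly 55. The 55 is a planning target with over-recruitment, so missing an exact split has almost no consequence.
- **That allocation is known to be simple.** Making allocation independent of diagnosis or other criteria rules out stratifying on participant characteristics. It does not clearly rule out blocks, a fixed-size list or separate lists per run, and an article may leave that detail to the full protocol. The figures in steps 4 and 5 are conditional for this reason.
- **That blocking by run and diagnosis is nearly free.** Diagnoses overlap, so a rule for the main one is needed. A run of 24 with three diagnoses has about 24 / 3 = 8 people per stratum, which leaves incomplete blocks. Small blocks in an open trial can also be guessed.

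The Feasibility section reports high feasibility after the first round, which also tells against calling the groups unworkable.

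**Conclusion.** The point holds as a moderate design improvement. It is not an error in N or power and not a source of bias. What the text establishes is that allocation takes no account of diagnosis and that the stated analysis adjusts for neither diagnosis nor run. The resulting chance of an imbalance of about 15 points or more between some pair of arms is roughly 10% to 26%, for assumed shares of 20% to 50%. Its effect on the comparison depends on how strongly diagnosis predicts change, which the documents do not give.

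The concern about uneven groups within a run is conditional on simple allocation and on run size: one arm is at least twice another in 43% of runs of 24, 33% of runs of 30 and 25% of runs of 36. Even then, average power falls only from 80% to about 79.5%.

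Because the analyst is unblinded, the adjustment should be fixed in advance. Covariates chosen after an imbalance has been seen would be hard to defend.

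**What to change.** 1. **Analysis.** Include main MINI-DIPS diagnosis, its interaction with time, and run as factors in the primary model. The interaction is needed because, in a repeated measures ANOVA, a between-person main effect alone does not adjust the comparison of change between arms. Fix beforehand the rule that assigns one main diagnosis to a person with several.
2. **Allocation in the remaining runs.** Use a list prepared in advance, with permuted blocks of varying size within run, concealed from those who screen and enrol. Runs already allocated stay as they are and are handled by the adjustment.
3. **Text.** Name the type of sequence and replace the sentence on independence from other criteria, for example: allocation is by concealed permuted blocks within run; diagnosis is not used in allocation and is adjusted for in the primary analysis.
4. **Optional.** Stratify by main diagnosis within run only if runs are large enough; otherwise the strata are too small to help much.

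The cost is one list per run, a rule for overlapping diagnoses and a few model degrees of freedom. The downside is slight predictability of blocks in an open trial, which varying sizes and concealment limit.
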